### Sample size

The primary outcome consists of the time to first flatus and the time to first defecation. Based on previous trials [24, 25] and clinical experience, the time to first flatus will be assumed to be 48 h and 64.8 h for the EA group and the control group, respectively, with a standard deviation of 21.6. Given a 2.5% two-sided significance, 80% power, and 10% drop rate, a sample size of 105 patients will be recruited, with 35 patients in each group. The time to first defecation will be assumed to be 86 h and 122 h for the EA group and the control group, respectively, with a standard deviation of 45. Given a 2.5% two-sided significance, 80% power, and 10% drop rate, a sample size of 90 patients will be recruited, with 30 patients in each group. In conclusion, 105 patients, with 35 patients in each group, will be recruited.

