### Primary outcome

The primary outcome is a composite endpoint consisting of the time to first flatus and the time to first defecation [34], which are defined as the time from the end of the operation to the first exhaust and defecation, respectively, and will be recorded in hours in the case report form by patients under the supervision of an assessor during hospitalization. The minimum clinical significance of the primary outcome is 12 h [27].

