### Statistical analysis

All statistical analyses will be performed according to the intention-to-treat (ITT) principle, which includes patients who will have received electroacupuncture at least once or who will have completed DSF for at least 1 day.

All paper data will be input into the electronic CRF and analyzed by SPSS 20. Measurement data will be presented as the mean ± standard deviation (M ± SD) or median and quartile spacing, and counting data will be presented as the composition ratio and percentage. Demographic and other baseline data will be compared by ANOVA and the chi-square test. The primary outcome and the time endpoints of the secondary outcomes will be compared by the Kaplan-Meier Breslow (generalized Wilcoxon) test. The incidence of pain, nausea, and abdominal distension; the frequency of vomiting; and the incidence of complications will be analyzed by the chi-square test or Mann-Whitney *U* test. Factors that may affect the results such as the stage and metastasis of colorectal will be recorded in the baseline. If these factors are unbalanced at baseline, we will use these factors as stratification factors to control the potential influence. The statistically significant *P* test level will be less than 0.025 for the primary outcome and less than 0.05 for the secondary outcomes. The primary outcome will be considered to be statistically different when both the first flatus time and the first defecation time are statistically different between the groups. The missing data will be filled using the last observation carry-over method. No additional, subgroup or interim analyses are planned for the trial.

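### The primary rule requires both flatus and defecation to be significant, but 35 per arm gives about 80% power only for each endpoint alone; for the rule itself power is about 66–74% per EA–control contrast

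*Protocol article*

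**What the plan says.** Three parts of the protocol article bear on this point.

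- **Primary outcome**: "The primary outcome is a composite endpoint consisting of the time to first flatus and the time to first defecation".
- **Sample size**: two separate calculations.
  - For flatus, "the time to first flatus will be assumed to be 48 h and 64.8 h for the EA group and the control group", "with a standard deviation of 21.6". The result is "Given a 2.5% two-sided significance, 80% power, and 10% drop rate, a sample size of 105 patients will be recruited", 35 per arm.
  - For defecation, "The time to first defecation will be assumed to be 86 h and 122 h for the EA group and the control group", "with a standard deviation of 45". With the same level, power and dropout, the result is "a sample size of 90 patients will be recruited, with 30 patients in each group".
  - The larger of the two, 105, becomes the trial size.
- **Statistical analysis**: the primary test level is 0.025, the test is Breslow (generalized Wilcoxon), and the primary outcome is "statistically different when both the first flatus time and the first defecation time are statistically different between the groups".

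The article gives no joint power, no correlation between the endpoints and no allowance for the both-required rule.

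**The concern.** Taking the larger of two sample sizes secures at least 80% power for each endpoint separately. It does not secure 80% for a decision that needs both, because the trial can fail on either one. The 80% that supports 105 patients therefore belongs to a different decision from the one the analysis section makes.

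The word composite hides this. A composite is one variable with one test and one power. Here two variables are tested and both must succeed, which makes them co-primary endpoints.

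At stake is how a negative result is read. A reader who takes the trial to have 80% power will give a null finding for ST25 or ST36 more weight than the design supports.

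**Working it through.** **Inputs** (Sample size section unless noted)

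- Flatus: difference 64.8 − 48 = 16.8 h, SD 21.6 h, standardised effect 0.778.
- Defecation: difference 122 − 86 = 36 h, SD 45 h, standardised effect 0.80.
- Two-sided level 0.025, so z = 2.2414. Power 80%, so z = 0.8416. Dropout 10%.
- 35 recruited per arm, so 35 × 0.9 = 31.5 evaluable per arm.
- Success rule: both endpoints significant (Statistical analysis section).
- Assumed, because the article does not give it: within-arm correlation ρ between the two times, taken from 0 to 0.8.

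**Step 1. Reproduce the plan's figure.** With n = 2 × [SD × (2.2414 + 0.8416) / difference]²:

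- Flatus: 2 × (21.6 × 3.083 / 16.8)² = 31.42 evaluable per arm, and 31.42 / 0.9 = 34.9. This gives 35 per arm and 105 in total, as stated.
- Defecation: 2 × (45 × 3.083 / 36)² = 29.70, so 30 per arm before dropout.

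The method is therefore a comparison of two means, one endpoint at a time. As a side point, the defecation figure of 90 matches only without the stated 10% dropout. With it, 29.70 / 0.9 = 33.0 (or 30 / 0.9 = 33.3), so 33–34 per arm and 99–102 in total. This does not change the 105.

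**Step 2. Power of each endpoint at 31.5 per arm.** With power = Φ(difference / [SD × √(2/31.5)] − 2.2414):

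- Flatus: 16.8 / (21.6 × 0.252) = 3.087, and Φ(0.845) = 80.1%.
- Defecation: 36 / (45 × 0.252) = 3.175, and Φ(0.933) = 82.5%.

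**Step 3. Power of the both-required rule.** This is the bivariate normal probability that both statistics exceed 2.2414. At ρ = 0 it is the product, 0.801 × 0.825 = 0.661.

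| ρ | Joint power, 31.5 evaluable per arm | Joint power, all 35 evaluable |
|---|---|---|
| 0 | 66.1% | 73.1% |
| 0.3 | 68.5% | 74.9% |
| 0.5 | 70.5% | 76.5% |
| 0.8 | 74.4% | 79.7% |
| 0.9 | 76.4% | 81.3% |

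Joint power cannot exceed the smaller single-endpoint power, 80.1% at the planned loss, and approaches it only as ρ approaches 1.

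**Step 4. Sensitivity.**

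- Simulated two-sample t-tests give slightly less: about 62–71% with 31 per arm and 64–73% with 32, for ρ from 0 to 0.8.
- If the times were normal, the rank test's efficiency factor of 0.955 would give 63%, 68% and 72% at ρ = 0, 0.5 and 0.8.
- If both acupoints have the full assumed effect and share the control arm, simulation puts the chance that both meet the rule at about 49–61%, and the chance that at least one does at about 82–88%.

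**Step 5. Size needed for 80% joint power with 10% dropout.** 40 evaluable per arm at ρ = 0 (45 recruited, 135 in total), 38 at ρ = 0.5 (43, 129) and 36 at ρ = 0.8 (40, 120).

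**The case against.** The strongest reply is that the Sample size section attaches 80% to each endpoint's own calculation and never claims it for the joint rule. The flatus sentence is arithmetically right, as Step 1 shows. That is fair: the fault is a mismatch between the sizing and the decision rule, not a slip in that sum. But the section offers these calculations as the justification for 105 patients, and a reader will take 80% as the trial's power for its primary outcome.

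Other points, and what stands of each:

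- **Dropout may cost less than 10%.** Data collection continues to discharge after patients stop treatment, and the test can handle censoring. With nobody lost, joint power is 73–80%, and this belongs beside the main range. The plan itself budgets for 10% loss, so 31.5 per arm remains the base case.
- **Either acupoint may succeed.** The hypotheses in the Background are worded as EA A or EA B against control, and the chance of at least one success is about 82–88%. But this requires both acupoints to have the full assumed effect, the sizing is for a single EA–control comparison, and the plan claims no either-arm power. Equally, no rule requires both arms to succeed, so the 49–61% should not be quoted without the 82–88%.
- **The Wilcoxon adjustment is uncertain.** The 0.955 factor holds for normal data; with skewed times a rank test may lose or gain. The conclusion does not rest on it.
- **It is called a pilot, and requiring both endpoints does not inflate false positives.** Both are true. Neither makes the power figure apply to the rule.
- **The 0.025 level already allows for multiplicity.** That level is built into the sizing and does not restore joint power.

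**Conclusion.** The concern holds. The power given for 105 patients is not the power of the trial's own primary decision. On the plan's effects, SDs, level and dropout, that power is about 66–74% per EA–control contrast for endpoint correlations from 0 to 0.8, and about 73–80% if no one is lost. An acupoint with the assumed effects would be missed 26–34% of the time at the planned dropout, roughly one in four to one in three, against the one in five that 80% implies.

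The size of the shortfall depends on the unstated correlation and on the normal approximation to a comparison of means. Its existence does not: flatus was sized to just 80%, so a second required endpoint leaves no reserve.

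**What to change.** Keep 105 patients and restate the claim in the Sample size section, for example:

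> With 35 patients per group and 10% dropout, power per endpoint is about 80% for time to first flatus and 82% for time to first defecation. Power for the primary rule, both endpoints significant at two-sided 0.025, is about 66–74% per EA–control contrast for an assumed endpoint correlation of 0 to 0.8 (about 73–80% with no dropout).

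In the Primary outcome section, replace the composite label with: two co-primary endpoints, both required. While editing, correct the defecation total of 90 to 99–102, or state that it excludes dropout.

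The cost is wording only: no extra patients and no change to design or test, but a less favourable stated power. If the sponsor wants 80% for the both-required rule, the price is about 120–135 patients in total, depending on the correlation. The restatement does not require that.

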### Statistical analysis

All statistical analyses will be performed according to the intention-to-treat (ITT) principle, which includes patients who will have received electroacupuncture at least once or who will have completed DSF for at least 1 day.

All paper data will be input into the electronic CRF and analyzed by SPSS 20. Measurement data will be presented as the mean ± standard deviation (M ± SD) or median and quartile spacing, and counting data will be presented as the composition ratio and percentage. Demographic and other baseline data will be compared by ANOVA and the chi-square test. The primary outcome and the time endpoints of the secondary outcomes will be compared by the Kaplan-Meier Breslow (generalized Wilcoxon) test. The incidence of pain, nausea, and abdominal distension; the frequency of vomiting; and the incidence of complications will be analyzed by the chi-square test or Mann-Whitney *U* test. Factors that may affect the results such as the stage and metastasis of colorectal will be recorded in the baseline. If these factors are unbalanced at baseline, we will use these factors as stratification factors to control the potential influence. The statistically significant *P* test level will be less than 0.025 for the primary outcome and less than 0.05 for the secondary outcomes. The primary outcome will be considered to be statistically different when both the first flatus time and the first defecation time are statistically different between the groups. The missing data will be filled using the last observation carry-over method. No additional, subgroup or interim analyses are planned for the trial.

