### Randomization and allocation concealment

Patients will be randomly assigned to the EA A, EA B, and control groups in a 1:1:1 ratio. The randomization sequence will be generated by an independent statistician who will not participate in the study using block randomization in SAS 9.3 software. The treatment allocation code will be placed in an opaque envelope labeled with a sequential number. After informed consent is obtained from an eligible patient, the acupuncturist will receive an opaque envelope and begin electroacupuncture treatment on the two EA groups.

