### Masking

Patients in the two EA groups, hospital staff (surgeons and nurses) assessors, and statisticians will be blinded to the group assignments, but the patients in the control group will not be blinded because of the particularity of the treatment. The acupuncturists will not be blinded.

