#### Control group

Patients in the control group will receive RSPC without acupuncture. At the end of the trial, if a patient is willing to contact us, we will give free acupuncture treatment.

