### Secondary outcomes

Secondary outcomes will include the length of the hospital stay; the time to first tolerance of liquid and semiliquid food; postoperative pain; postoperative use of analgesics; postoperative nausea and vomiting; the time to first walk independently; postoperative distension of the abdomen; and adverse events.

The length of the hospital stay is defined as the time from the end of the operation to discharge. The time to first tolerance of liquid and semiliquid food is defined as the time from the end of the operation to the first tolerance of the aforementioned two kinds of food without gastrointestinal adverse reactions. The time to first walk independently is defined as the time from the end of the operation to the first time the patient can get out of bed and ambulate. Postoperative pain will be evaluated regularly at three fixed times per day using the visual analog scale (VAS, from 0 to 10), and the three scores will be averaged. The higher the score is, the more severe the indication of pain and nausea is. Vomiting, nausea, and abdomen distension will be counted once, daily. The abovementioned outcomes will be recorded by the patient on a daily assessment form (DSF) during hospitalization.

Adverse events include postoperative complications and adverse acupuncture events. Postoperative complications, such as fever, intestinal edema, and intestinal anastomotic fistula, will be recorded and graded according to the Clavien-Dindo classification (Table 2) by the assessors. If patients have serious complications after surgery, the participants will be asked to discontinue the trial, and the doctor will administer appropriate treatment. Adverse acupuncture events include subcutaneous hematoma, continuous acupuncture afterfeeling, and itching at the sites of needle insertion and will be recorded by the assessors.

**Table 2 Tab2:** Clavien-Dindo classification

**Grade 1**	Any deviation from the normal postoperative course without the need for pharmacologic treatment or surgical, endoscopic, and radiologic interventions. Allowed therapeutic regimens are drugs as antiemetics, antipyretics, analgetics, and diuretics, and electrolytes and physiotherapy. This grade also includes wound infections opened at the bedside
**Grade 2**	Requiring pharmacologic treatment with drugs other than such allowed for grade I complications. Blood transfusions and total parenteral nutrition are also included

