### Data management

All data will be collected in case report forms (CRFs) that have been created by study members and will be entered into electronic record form by two independent researchers to ensure the accuracy of the data from the operation day to the discharge day. The investigators will continue to collect data on patients in the ward who have fallen off treatment for as long as possible until the end of the trial (discharge). The data collectors will be trained to fill out the CRFs to ensure the accuracy of the data. Paper files, including the original CRFs (including the baseline data and DSF data) and consent forms, will be kept for more than 5 years after publication. All final data will only be accessed by the study staff and kept strictly confidential. Readers and reviewers who have questions or want to check the original data can contact the corresponding author. Private patient information, including names, home addresses, and telephone numbers, will be kept confidential at all times.

Moreover, an independent Data and Safety Monitoring Board (DSMB) will be set up to review the trial data every month and determine whether the patient needs to discontinue from this trial in the event of complications and seek medical attention. The members of the DSMB are selected and appointed by the sponsor and include physicians and ethicists who are not involved in the study. The role of the DSMB is to help sponsors maintain a rigorous study design, give appropriate attention to subject protection, review and evaluate clinical efficacy and safety data collected during the study, and evaluate cumulative reports of serious adverse events.

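### The analysis set called intention-to-treat is a modified set, and its entry rule is not the same in the control arm as in the two electroacupuncture arms

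*Protocol article*

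**What the plan says.** The Statistical analysis section of the protocol article opens with the claim "All statistical analyses will be performed according to the intention-to-treat (ITT) principle". The same sentence then says that this "includes patients who will have received electroacupuncture at least once or who will have completed DSF for at least 1 day". No other section defines a set of all randomised patients, and the section rules out additional analyses.

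Four other places bear on how the rule works:

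- Randomization and allocation concealment: "Patients will be randomly assigned to the EA A, EA B, and control groups in a 1:1:1 ratio".
- Control group: "Patients in the control group will receive RSPC without acupuncture".
- Masking: "the patients in the control group will not be blinded because of the particularity of the treatment".
- Secondary outcomes: the daily outcomes "will be recorded by the patient on a daily assessment form (DSF) during hospitalization".

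Two further statements affect what data would exist for a patient outside the set. Under Primary outcome, the flatus and defecation times "will be recorded in hours in the case report form by patients under the supervision of an assessor during hospitalization". Under Data management, the plan is to "continue to collect data on patients in the ward who have fallen off treatment for as long as possible until the end of the trial", which ends at discharge.

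**The concern.** Intention-to-treat means that all randomised patients are analysed in the arm they were assigned to. Here membership depends on what happens after assignment, and one of the two qualifying events cannot occur in one of the three arms. The label and the rule therefore disagree.

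Randomisation makes the arms comparable as assigned. Once patients can be removed afterwards, and the removal rule is looser in two arms than in the third, that comparability is no longer guaranteed for the patients left in the analysis. The control patients also know their allocation, and their only way into the set is a form they fill in themselves. The extra route open to the other arms is a session given by an acupuncturist and recorded by study investigators. The rule governs every analysis in the trial, and a larger sample would not repair a loss of comparability.

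**Working it through.** **1. The entry rule by arm.** Put the set definition beside the description of the control arm:

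| Patient after randomisation | EA at ST25 or ST36 | Control |
|---|---|---|
| At least one DSF day | in | in |
| No DSF day, at least one session | in | cannot occur |
| No DSF day, no session | out | out |

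Every control with no DSF day falls in the bottom row. An EA patient with no DSF day does so only if no session was given either. The arms thus differ only for patients with no DSF day at all.

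**2. Inputs for a sense of scale.** From Sample size: 35 per group; control mean for flatus 64.8 h against 48 h (difference 16.8 h), SD 21.6 h; control mean for defecation 122 h against 86 h (difference 36 h), SD 45 h; two-sided level 0.025, power 80%, dropout 10%. From Primary outcome: minimum important difference 12 h. The document gives no rate of missing DSF, so the number excluded, k, is an assumption throughout.

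The group size can be reproduced: n = 2 × (2.241 + 0.842)² × 21.6² / 16.8² = 31.4, and 31.4 / 0.9 = 34.9, which rounds up to the stated 35. (Rounding to 32 before the dropout step gives 36.) This only confirms the inputs; the point does not rest on it.

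**3. Moderate case.** Suppose k of 35 controls are excluded and their mean differs from that of the retained controls by one SD. The retained mean then differs from the mean of all 35 by SD × k / 35.

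| k | Flatus: 21.6 × k/35 | Defecation: 45 × k/35 |
|---|---|---|
| 1 | 0.6 h | 1.3 h |
| 2 | 1.2 h | 2.6 h |
| 3 | 1.9 h | 3.9 h |
| 4 | 2.5 h | 5.1 h |

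**4. Extreme bound.** Suppose the excluded controls are exactly the k fastest of 35. The mean of the rest rises by SD × S / (35 − k), where S is the sum of the k largest expected standard normal order statistics for 35 observations (2.107, 1.690, 1.448).

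- k = 2: S = 3.797. Flatus 21.6 × 3.797 / 33 = 2.5 h; defecation 45 × 3.797 / 33 = 5.2 h.
- k = 3: S = 5.244. Flatus 21.6 × 5.244 / 32 = 3.5 h; defecation 45 × 5.244 / 32 = 7.4 h.

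If they are exactly the k slowest, the mean falls by the same amounts. As a share of 12 h, the k = 3 figures are 3.5/12 = 30% and 7.4/12 = 61%. If exclusion is unrelated to recovery, the expected shift is zero.

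**5. Power.** With 35 EA patients and 35 − k controls, power for flatus is Φ(16.8 / (21.6 × √(1/35 + 1/(35 − k))) − 2.241). For k = 0 this is Φ(3.254 − 2.241) = 84.4%; for k = 4 it is Φ(3.154 − 2.241) = 81.9%. The issue is comparability, not power.

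Steps 3 to 5 treat times as normal and compare means. The planned test is the Breslow (generalized Wilcoxon) comparison, so these figures show scale and do not predict the test result.

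**The case against.** The strongest reply is that the rule will seldom exclude anyone. The two conditions are alternatives, one DSF day is enough, and the patients are in hospital. The primary times are recorded with an assessor supervising, and data collection on the ward continues after treatment stops. All of this stands, and it is why the effect is probably small. It does not change the definition: continued collection supplies data but does not bring a patient into the set.

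A reader might infer that unblinded controls are likely to stop filling in the form, so that the bias is real and runs in a known direction. The article does not support this. It reports no completion rates. Patients consent before randomisation after being told the procedures, controls are offered free acupuncture at the end, and EA patients may withdraw too. Knowing the allocation makes selective non-completion possible; it does not show that it will happen.

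A reader might also infer that any control who withdraws on learning the allocation is dropped. That is true only if no DSF day was completed; a control who leaves after one day of the form is kept. An EA patient who leaves before both the first session and the first form is excluded just as a control would be.

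Nor should the 2.5 to 7.4 h figures be read as an expected bias. They require perfect selection on recovery speed. A patient who leaves before completing any form would mostly do so before first flatus, which makes such selection implausible.

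Finally, the remedy may add little. If a patient with no DSF also has no recorded event time, censoring near time zero contributes almost nothing. The article places the primary times in the case report form and also counts DSF data as part of the original case report forms. It is therefore unclear whether a primary time could exist without a DSF day. If it could, the present rule would discard a control with a usable primary outcome.

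An unseen analysis plan does not answer the point, because the article states the definition itself and that definition contradicts its label.

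**Conclusion.** The point holds as a defect in a stated rule. The set is a modified intention-to-treat set, it depends on events after randomisation, and its entry condition differs by arm. This follows from the text alone and needs no assumption.

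The consequence is uncertain and probably small. Assuming 1 to 4 of 35 controls are excluded and differ from the rest by one SD, the control mean shifts by 0.6 to 2.5 h for flatus, against a planned difference of 16.8 h, and by 1.3 to 5.1 h for defecation, against 36 h. The extreme bounds with 2 or 3 excluded are 2.5 to 3.5 h and 5.2 to 7.4 h, below the 12 h minimum important difference. The direction cannot be stated. The rule should be corrected, but nothing in the document shows that it would by itself overturn the trial's conclusion.

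**What to change.** Replace the set definition with one sentence: the primary analysis includes all randomised patients, analysed in the arm to which they were assigned. For flatus and defecation, use any times entered in the case report form under the continued ward collection already planned, and right-censor patients without an event at their last observation. The time-to-event method already chosen accommodates this. Carrying the last observation forward cannot help a patient with no DSF day, who has no form entry to carry.

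If the present rule is kept, call it a modified intention-to-treat set, use it only as a sensitivity analysis, and report by arm how many randomised patients it leaves out.

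The cost is a change of wording, with no extra patients or visits. The downside is that patients with no recorded data add almost no information when censored early. The change makes the comparison follow the randomisation; it does not recover data that were never collected.

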We assume that electroacupuncture at ST25 or ST36 can promote recovery from POI. Accordingly, we have designed a pilot trial to evaluate the therapeutic potential of electroacupuncture at ST25 (EA A) or ST36 (EA B) compared to a control on POI after laparoscopic surgery for colorectal cancer.

The hypotheses are as follows.

H0: Effect of EA A or EA B = effect of the control group

H1: Effect of EA A or EA B ≠ effect of the control group

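### The primary success rule does not require both endpoints to improve in the same EA-control comparison, so a positive result need not mean that either acupoint works on both

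*Protocol article*

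**What the plan says.** Patients are randomized 1:1:1 to EA at ST25 (EA A), EA at ST36 (EA B) or control. The primary outcome combines time to first flatus and time to first defecation.

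- **Hypotheses (Background):** "H0: Effect of EA A or EA B = effect of the control group" and "H1: Effect of EA A or EA B ≠ effect of the control group".
- **Sample size:** flatus is planned at "48 h and 64.8 h for the EA group and the control group, respectively, with a standard deviation of 21.6", and defecation at 86 h and 122 h with a standard deviation of 45. Each uses two-sided 2.5% significance, 80% power and 10% dropout. One EA group is described, without saying which.
- **Test (Statistical analysis):** the primary outcome "will be compared by the Kaplan-Meier Breslow (generalized Wilcoxon) test". The article does not say whether this is one three-group test or a set of two-group tests.
- **Level (Statistical analysis):** the "test level will be less than 0.025 for the primary outcome and less than 0.05 for the secondary outcomes".
- **Success rule (Statistical analysis):** the primary outcome counts as different "when both the first flatus time and the first defecation time are statistically different between the groups".

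**The concern.** With three arms, a difference between the groups can mean several things. The wording fits a three-group test on each endpoint. It also fits flatus differing for EA A and defecation for EA B, or any pair of arms differing. None of these requires one acupoint to improve both endpoints, and none requires the difference to favour EA.

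The Discussion gives the aim as finding out whether EA at a single acupoint promotes recovery. A result assembled from two acupoints does not answer that. An unsettled rule also leaves the reading to be chosen after the results are known.

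The 0.025 level adds to the uncertainty, because the article does not say what it is split over. A rule that needs both endpoints requires no split across endpoints. The level therefore makes sense only as a split across the two EA-control comparisons.

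**Working it through.** **1. The planned sample size.** For one EA arm against control at two-sided 0.025 and 80% power, n per group = 2(z₁ + z₂)²(SD/difference)², with z₁ = 2.241 and z₂ = 0.842.

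- Flatus: 2 × (3.083)² × (21.6/16.8)² = 31.42, and 31.42/0.9 = 34.92, so 35 per group. This reproduces the plan.
- Defecation: 2 × (3.083)² × (45/36)² = 29.70, so 30 before dropout and 33-34 after it. The stated 30 matches only without dropout. This does not affect the final 35, which flatus drives.

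The design was therefore sized as a two-group EA-control comparison at 0.025.

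**2. Inputs for testing the rule.** Effects are 16.8 h (SD 21.6) for flatus and 36 h (SD 45) for defecation, from Sample size. Evaluable patients per arm are 35 × 0.9 = 31.5. The correlation between endpoints is not given, so 0, 0.5 and 0.8 are assumed. Outcomes are taken as normal and uncensored.

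**3. Illustration: EA A moves only flatus, EA B only defecation.** No acupoint improves both.

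*Three-group test.* With one arm shifted, the noncentrality is n × (difference/SD)² × 2/3 on 2 degrees of freedom.

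- Flatus: 31.5 × (16.8/21.6)² × 2/3 = 12.7, power 0.844.
- Defecation: 31.5 × (36/45)² × 2/3 = 13.4, power 0.867.
- Both at correlation 0: 0.844 × 0.867 = about 0.73.

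*EA-control tests, a different arm allowed per endpoint.*

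- Flatus: 16.8/(21.6 × √(2/31.5)) = 3.087, and 3.087 − 2.241 = 0.846 gives power 0.801.
- Defecation: 36/(45 × √(2/31.5)) = 3.175, and 3.175 − 2.241 = 0.934 gives power 0.825.
- Product at correlation 0: 0.66. Chance findings in the inactive contrasts raise it to about 0.68.

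Simulation over the three correlations (400,000 trials each, normal approximation), beside a rank-test simulation (32 per arm, 10,000 trials each; without censoring the Breslow test corresponds to these rank tests):

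| Reading of the rule | Normal approximation | Rank tests |
|---|---|---|
| Three-group test on each endpoint | 71-73% | 65-68% |
| EA-control tests, any EA arm per endpoint | 67-70% | 61-64% |
| Any pair of arms | 84-85% | 80-81% |
| Same EA arm better than control on both | about 2% | about 2% |

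**4. Direction.** If both EA arms were slower than control by the planned amounts, the rank-test simulation meets the rule in 67-75% of trials (three-group) or 81-85% (any pair). Requiring benefit reduces this to 0%.

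**5. No effect anywhere.** The rule is met in 0.1-0.7% of trials (three-group) and 0.3-2.6% (any pair) with rank tests. The normal approximation gives 0.4-2.8% for any pair.

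**6. Holm instead of a fixed 0.025 per contrast.** The p-value for a contrast is the larger of its two endpoint p-values. At correlation 0.5 with both arms effective, power per contrast rises from 70.5% to 76%, and power for both arms from 56% to 67%. If only one arm works, power for it stays at about 70.5%. The chance of at least one success is unchanged.

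**The case against.** The strongest defence is that the article read as a whole points to the sensible rule. The hypotheses set EA against control, and the sample size is for an EA-control comparison at the same 2.5% level. The Discussion speaks of a single acupoint. EA A versus control and EA B versus control, each at 0.025 with both endpoints required, is a natural reading. A condensed article may also leave the choice of three-group or pairwise test to a fuller document.

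Much of this stands. The hypotheses and sample size make EA A versus EA B an unlikely primary contrast, so the 84-85% figure belongs to the least likely reading. But the success rule is stated here, not deferred. The joined hypothesis still lets one arm supply flatus and the other defecation, and its two-sided alternative sets no direction. Confined to EA-control tests, the illustration still gives 67-70%.

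A reader might infer three stronger points that the documents do not support:

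- *That the rule fails to control type I error.* Under the global null it is met in at most about 3% of trials, for correlations up to 0.8.
- *That a misleading result is likely.* The split-effect case is constructed. The article plans both effects for its EA group and nowhere predicts that each acupoint moves one endpoint only.
- *That a fixed 0.025 per contrast is wrong or always wastes power.* It is a valid split. Holm gains only when both acupoints work.

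**Conclusion.** The concern holds as a fault of attribution. The stated rule can be met when neither acupoint improves both endpoints, and even when both arms do worse, although few readers would present the latter as success. With the planned effects split across arms, 67-73% of trials would meet it under the two more plausible loose readings, against about 2% when one EA arm must benefit on both. These figures rest on the article's effect sizes, 31.5 evaluable per arm, an assumed correlation of 0 to 0.8, and normal, uncensored times. Rank tests give values about 5 or 6 points lower and the same conclusion. The rule should be corrected because it fixes what the trial may claim.

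**What to change.** Reword the success rule along these lines, before unblinding:

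- There are two primary contrasts, EA A versus control and EA B versus control, each analysed with two-group Breslow tests.
- A contrast succeeds only if both endpoints are significant in favour of EA within that contrast. Its p-value is the larger of its two endpoint p-values.
- The 0.025 level is the split of 5% over the two contrasts, with no further split over endpoints. The contrasts are tested by Holm: the smaller p-value at 0.025 and, if that succeeds, the other at 0.05.
- EA A versus EA B is descriptive.

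The essential parts are the named contrasts, the same-arm requirement and the direction. Holm is an added gain: it keeps the 5% familywise level and never loses power against the fixed split. The cost is analysis wording only. The sample size stays at 35 per group, since it already rests on one EA-control comparison at two-sided 0.025.
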